#### Primary outcome

The primary outcome is the absolute difference between the 4FREAR for each intervention.

The clinician will measure the real-ear aided response of each hearing aid following the NZAS Best Practice Guidelines using a Natus Aurical Freefit and Otometrics Otosuite PMM module for soft (55 dB), medium (65 dB), and loud (75 dB) signal outputs using the International Speech Test Signal, and an on-ear Maximum Power Output measurement at 85 dB [19].

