**Results:**

Data will compare the four-frequency average real-ear aided response (4FREAR) for hearing aids programmed in-clinic and hearing aids programmed remotely, after participant-directed gain adjustments. Secondary measures will assess clinically significant differences in estimated speech intelligibility, hearing-related quality of life, hearing aid benefit, sound quality and preference, and speech-in-noise ability.

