Self-reported outcomes are reported to be the same for people who had an in-clinic hearing aid fitting and follow-up process and those who had remote follow-up appointments [18], but it is important to also consider objective clinical measures. Furthermore, Tao et al. included a facilitator, present in the subject’s home, to assist the remote audiologist, with a laptop to connect to the hearing aid and provide a video and audio link. More recent updates in hearing aid technology allow audiologists to use individual’s smartphones for a video and audio link as well as connecting directly to the individual’s hearing aids via apps (for example, myPhonak by Phonak, TeleHear by Starkey Hearing Technologies and Smart 3D by GN ReSound). This negates the need for a facilitator and requires the individual to take a more active role in the appointment.

In New Zealand, the best practice guidelines for tuning hearing aids is to adjust the output to prescribed targets (most commonly the National Acoustics Laboratory Non-Linear 2 prescription (NAL-NL2)), verified with objective clinic measurements that assess the hearing aid output by frequency across multiple signal input levels, adjusted to the ear canal acoustics of the individual [19]. This measurement can be performed in a test box or as a real-ear measurement (REM) with the hearing aids positioned in the individual’s ear canal. A real-ear aided response (REAR) is obtained, which is a measurement of the sound levels in the ear canal accounting for the input signal, the individual ear canal acoustics and the hearing aid amplification. Audiologists adjust the output of the hearing aid until the REAR matches prescribed targets. The New Zealand Audiological Society allows a tolerance from the prescribed targets of + / − 5 dB for frequencies up to 2000 Hz and + / − 8 dB for 3000 and 4000 Hz [19]. In practice, audiologists also use a person’s subjective report to adjust hearing aid settings: comments such as “tinniness” or “sharpness” may lead to decreases in high-frequency amplification; reports of cutlery and crockery being unbearably “clattery” may lead to overall reduction in volume in quieter environments. Hearing aids programmed using manufacturer’s initial fit without REMs show statistically poorer self-reported listening ability and listening in noise, but the effect is small and it is not clear whether there is a clinically significant benefit [20].

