### Sample size {14}

Sixty participants (thirty per group) will be recruited for the trial. This will provide 90% power at the 5% significance level to detect an overall clinically meaningful difference of 5 dB 4FREAR and allow for up to 10% attrition.

Power analysis was conducted by selecting a random sample of patients from a clinical register and using the variance in REM scores to estimate the expected variance in the research. Power analysis for a 5-dB non-inferiority limit (the acceptable variance in REMs according to the NZAS Best Practice Guidelines) in a continuous outcome in a non-inferiority trial with an alpha level of 5% and 90% power indicates a total sample size of 54 (27 per group). We propose a sample size of 60, which will allow 30 in each hearing loss group and therefore a repeated measures analysis on groups of 30.

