## Statistical methods

### Statistical methods for primary and secondary outcomes {20a}

The difference in REAR measures between interventions will be used as the primary outcome. The data will be modelled as a fully factorialised 5-way mixed-measures ANOVA with repeated measured being: ear (right and left), frequency (500, 1000, 2000, 4000 Hz), REM signal input level (55 dB, 65 dB, 75 dB), and fitting method (in-clinic or remote); and level of hearing loss (mild or moderate) as a between-participant factor.

Secondary analyses of speech intelligibility, hearing-related quality of life, hearing aid benefit, sound quality and preference, and speech-in-noise ability will be conducted in the same way. In the analyses, a main or interaction effect involving fitting method will provide evidence that the in-clinic and remote fitting approaches led to differences in the variables involved. Interactions will be explored using testing of simple effects using follow-up ANOVAs and graphical representations of data including error bars based on the standard error of the mean difference between the points, to represent the repeated measured nature of these variables, and using the standard error of the mean for analysis related to level of hearing loss.

Given the statistical power inherent in the data analysis (repeated measures approach), the sample size should be sufficient. To ascertain the clinical importance of the difference observed at a statistical level, a criterion of + / − 5 dB will be applied to REAR measures, in accordance with best practice guidelines. The secondary outcomes do not have a convention associated with clinical importance, so any statistical effects observed will be discussed in terms of the specific measure and meaningful outcomes in previous research as well as making comparisons based on confidence intervals.

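### The primary outcome is defined in two ways, any of 16 ANOVA terms counts as a difference, and the flat 5 dB limit does not match the guideline as the protocol quotes it

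*Protocol article*

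**What the plan says.** **The outcome.** Under Primary outcome: "The primary outcome is the absolute difference between the 4FREAR for each intervention". The abstract (Results) makes 4FREAR an average over four frequencies: "Data will compare the four-frequency average real-ear aided response (4FREAR) for hearing aids programmed in-clinic and hearing aids programmed remotely". Sample size {14} also expresses the 5 dB effect in 4FREAR.

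**The analysis.** Statistical methods {20a} has a different outcome: "The difference in REAR measures between interventions will be used as the primary outcome". It continues: "The data will be modelled as a fully factorialised 5-way mixed-measures ANOVA". The repeated factors are ear, "frequency (500, 1000, 2000, 4000 Hz"), input level (55, 65, 75 dB) and fitting method. Level of hearing loss is the between-participant factor. The reading rule is that "a main or interaction effect involving fitting method will provide evidence that the in-clinic and remote fitting approaches led to differences" in the variables concerned. A flat criterion of plus or minus 5 dB on REAR measures then decides clinical importance and is attributed to best practice guidelines.

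**The threshold.** Sample size {14} calls the 5 dB non-inferiority limit "the acceptable variance in REMs according to the NZAS Best Practice Guidelines". Background {6a} describes the same guideline differently: "The New Zealand Audiological Society allows a tolerance from the prescribed targets of" 5 dB either way up to 2000 Hz, and 8 dB either way at 3000 and 4000 Hz.

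**The concern.** The trial is described as a non-inferiority trial, so its conclusion rests on one contrast compared with one margin. The article leaves both open.

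- The outcome is a four-frequency summary in one section and REAR by frequency in another. The word absolute appears only in the first.
- The analysis gives 16 routes to evidence of a difference, of which one addresses 4FREAR.
- The limit is credited to a guideline which, as quoted, concerns another quantity (distance of one fitting from its target) and has another value at one of the four analysed frequencies.

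The same data could then be read as supporting or not supporting remote fitting, depending on which definition, term or tolerance is used. The article says the result is to inform best practice guidelines, so this should be settled before the data are seen.

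**Working it through.** **1. The plan's own figure.** Inputs from Sample size {14}: limit 5 dB, alpha 5% (sidedness not given), power 90%, total 54 (27 per group), 60 recruited. The usual parallel-group formula is n per group = 2 × SD² × (z(1−α) + z(0.90))² / 5². No SD is stated, so 54 cannot be reproduced. Solving backwards:

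- One-sided 5%: 27 per group needs an SD of 6.16 to 6.28 dB. Check at 6.277: 2 × 39.40 × (1.645 + 1.282)² / 25 = 27.0.
- One-sided 2.5%: 5.56 to 5.67 dB.
- If 54 is instead a paired sample: an SD of differences of 11.3 to 12.6 dB.

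The attrition step does reproduce: 54 / 0.90 = 60.

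**2. Terms involving fitting method.** A full factorial in five factors has 2⁵ − 1 = 31 effects. Those containing fitting method number 2⁴ = 16: one main effect and 15 interactions.

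**3. Which term is the 4FREAR contrast.** In balanced data the fitting-method main effect is the mean of remote minus in-clinic REAR over ears, frequencies and input levels. Averaging over the four frequencies gives 4FREAR, so this term is the signed 4FREAR difference averaged over ears and levels. The 15 interactions ask whether that difference varies by ear, frequency, level or degree of loss.

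**4. The threshold, side by side.**

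| | Background {6a} | Sample size {14} and {20a} |
|---|---|---|
| Compared quantities | one fitting with its target | one fitting with the other |
| 500, 1000, 2000 Hz | 5 dB | 5 dB |
| 4000 Hz | 8 dB | 5 dB |

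The quoted tolerances average (5 + 5 + 5 + 8) / 4 = 5.75 dB over the four frequencies. Two fittings that each meet the quoted tolerance can differ by up to 5 + 5 = 10 dB at 2000 Hz, so a from-target tolerance does not by itself give a between-fitting limit.

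Two constructed examples of remote minus in-clinic at 500, 1000, 2000 and 4000 Hz:

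- −1, 0, −2, −7 dB: the 4FREAR difference is −10 / 4 = −2.5 dB, inside 5 dB. At 4000 Hz, 7 dB exceeds the flat 5 dB but not 8 dB.
- +6, +6, −5.5, −6.5 dB: the 4FREAR difference is 0, yet every single-frequency difference exceeds 5 dB.

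**5. If absolute means magnitude.** Assume normal paired differences with mean 0 and standard deviation SD_d. The mean magnitude is SD_d × √(2/π) = 0.798 × SD_d, which reaches 5 dB at SD_d = 5 / 0.798 = 6.27 dB. In 20,000 simulated trials with N = 54, the table shows how often the 90% confidence interval of the signed mean lay within 5 dB either way, and how often the one-sided 95% upper bound of the mean magnitude lay below 5 dB.

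| SD_d (dB, assumed) | Mean magnitude (dB) | Signed passes | Magnitude passes |
|---|---|---|---|
| 4 | 3.2 | 100% | 99.9% |
| 5 | 4.0 | 100% | 76% |
| 6 | 4.8 | 100% | 14% |
| 6.28 | 5.0 | 100% | 6% |
| 8 | 6.4 | 99.6% | 0.01% |

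Where SD_d lies is unknown. From SD_d = SD × √(2(1 − ρ)) with SD 5.67 to 6.28 dB, a within-person correlation ρ of 0.5 gives 5.7 to 6.3 dB, and 0.9 gives 2.5 to 2.8 dB.

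**The case against.** Several points on the other side stand.

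- Absolute difference often means a plain, non-relative difference in dB. The abstract, {20a} and the non-inferiority design fit that reading, and nothing in the article sets a limit on a mean magnitude. Step 5 then falls away.
- The ANOVA does contain the 4FREAR contrast, and exclusion of cases with missing data would keep it close to balanced.
- The rule on main and interaction effects follows a sentence on secondary outcomes, and the 5 dB criterion is applied afterwards to judge clinical importance. But those outcomes are to be analysed in the same way, so the rule reads as covering both, and nothing singles out the main effect as the deciding term.
- At 4000 Hz a flat 5 dB is stricter than the quoted 8 dB, and 5 dB is below the 5.75 dB average. Against those figures it does not favour remote fitting. The fault is the attribution.

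Two stronger readings are tempting. A reader might infer that the trial will declare equivalence while 43% of participants differ by more than 5 dB. That figure needs SD_d = 6.28 dB, hence a parallel-group back-calculation at one-sided 5% and a correlation of 0.5, none of which the article states. At a correlation of 0.9 the share is 5% to 8%. A reader might also infer that cancelling of positive and negative differences is itself an error. It is a property of any mean difference; agreement within individuals is another question, which the trial need not make primary.

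**Conclusion.** Two conflicts hold on the text alone, with no assumption about variability. First, Primary outcome and {20a} name different primary outcomes, and the analysis lets 16 terms speak for a difference when one corresponds to 4FREAR. Second, Sample size {14} and {20a} attribute a flat between-fitting 5 dB to a guideline that Background {6a} quotes as a from-target tolerance of 8 dB at 4000 Hz.

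A third conflict is conditional. Only if absolute means magnitude can the stated outcome and the ANOVA give opposite answers, and then only with an SD_d above about 4 dB, usually from about 6 dB, taking a true mean difference of zero and normal differences. The documents settle neither the word nor the SD, so opposite answers are a possibility and not a prediction. Which tolerance is clinically right is not judged here.

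**What to change.** 1. Name one primary contrast in both sections: the signed within-participant difference, remote minus in-clinic, in 4FREAR, stating how the two ears and three input levels are combined. Judge it by its confidence interval against the margin.
2. Make the 15 fitting-method interactions secondary, and say that they do not decide the primary conclusion.
3. Reword absolute so that it cannot be read as magnitude.
4. Reconcile Background {6a}, Sample size {14} and {20a}. Either present 5 dB on the mean 4FREAR difference as the trial's own margin, with its own justification, or match the criterion to the guideline as quoted, including what is compared with what.
5. Optional: describe individual differences per frequency, for example by limits of agreement. A pass rate that applies the from-target tolerance between two fittings would repeat the problem in point 4.

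The cost is wording in the protocol and analysis plan. No new measurement is needed.

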#### Secondary outcomes

Secondary outcome measures include:*Estimated speech intelligibility* measured by the Speech Intelligibility Index (SII) of each hearing aid fitting. An SII of zero indicates no intelligible speech and a score of one indicates all speech information is available to the participant. The REAR allows an SII to be calculated for each signal strength, allowing for comparison between interventions.*Hearing-related quality of life* measured using the Hearing Handicap Inventory for Adults (HHIA), a 25-item questionnaire that measures hearing-related QOL across social and emotional subdomains [27].*Hearing aid benefit* measured using the Abbreviated Profile of Hearing Aid Benefit (APHAB), a 24-item questionnaire that measures hearing aid benefit across four subscales: ease of communication (EC), reverberation (RV), background noise (BN), and aversiveness (AV)*Sound quality and preference* measured on 5-point Likert scales. Participants are asked to rate the overall sound quality of each intervention, and rate their preference between the interventions.*Process acceptability* (how likely the participant is to recommend the process to another person) measured as a net promotor score for each intervention.*Speech-in-noise ability* measured for each intervention with an unaided and aided quick speech-in-noise (QSIN) test. QSIN will be performed according to the QSIN user guide in a calibrated testing room with speech and background noise (four-speaker babble) presented from a single speaker in front of the participant at a level of 65 dB HL. A QSIN score for each intervention will be calculated from the average SNR loss across 3 standard test lists.

### Participant timeline {13}

Figure 2 shows the schedule of enrolment, interventions, and assessments.

**Fig. 2 Fig2:**
[figure not shown]
Schedule of enrolments, interventions and assessments

### Sample size {14}

Sixty participants (thirty per group) will be recruited for the trial. This will provide 90% power at the 5% significance level to detect an overall clinically meaningful difference of 5 dB 4FREAR and allow for up to 10% attrition.

Power analysis was conducted by selecting a random sample of patients from a clinical register and using the variance in REM scores to estimate the expected variance in the research. Power analysis for a 5-dB non-inferiority limit (the acceptable variance in REMs according to the NZAS Best Practice Guidelines) in a continuous outcome in a non-inferiority trial with an alpha level of 5% and 90% power indicates a total sample size of 54 (27 per group). We propose a sample size of 60, which will allow 30 in each hearing loss group and therefore a repeated measures analysis on groups of 30.

### Recruitment {15}

Recruitment will take place through the University of Auckland Hearing and Tinnitus Clinic and through private audiology clinics in the Auckland region. Recruitment will be via flyers and posters in clinic and on social media (Facebook and Instagram) networks. Posters will also be disseminated through audiologist networks so that they can invite people to participate in the study.

## Assignment of interventions: allocation

### Sequence generation {16a}

Eligible participants will be grouped according to degree of hearing loss (mild and moderate, according to WHO classifications [1]) to ensure an even spread of hearing levels between intervention groups. Participants within each hearing loss group will be assigned a random number as per a computer-generated randomisation schedule, then allocated to group A or B in the order ABAB, with an allocation ratio of 1:1, by a clinical research assistant.

### Concealment mechanism {16b}

Participants are assigned to one of the intervention groups but the group is concealed from them. They will not be aware of which fitting method they are trialling at any stage. Clinicians are not aware of which groups the participants have been assigned. A research assistant will allocate participants and will deidentify the hearing aid fitting files within Noah software. Each participant will have 2 hearing aid files (intervention A and B), and it will not be apparent to the researcher which intervention setting is being used at any time. The researcher will not know which group a participant is allocated by the research assistance until after the research is complete, at which point the research assistant will share the electronic records.

### Implementation {16c}

All participants who meet the eligibility criteria and complete the in-clinic and remote hearing aid fitting process will be randomised and assigned to an intervention group by a trained clinical research assistant. The research assistant will generate the allocation sequence.

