#### Initial in-clinic hearing aid fitting

For the initial in-clinic hearing aid fitting, participants will be fit binaurally with premium-level, rechargeable, receiver-in-the-canal hearing aids. The receiver and dome configuration will be chosen using standard clinical procedures and be consistent for each participant for the duration of the study. The hearing aids will be programmed through the manufacturer’s software to 100% acclimatisation using the National Acoustics Laboratory Non-Linear 2 (NAL-NL2) prescription targets for long-term hearing aid wearers.

REAR will be verified using a Natus Aurical Freefit and Otometrics Otosuite PMM module, with the gain settings adjusted through hearing aid software to meet NAL-NL2 targets for soft (55 dB), medium (65 dB), and loud (75 dB) stimuli using the International Speech Test Signal. On-ear measurement of maximum power output will be measured at 85 dB to ensure estimated uncomfortable loudness levels are not exceeded.

Where hearing aid programming features are available for an in-clinic session but are not available for a remote session, these will be removed from the in-clinic fitting protocol to maintain blinding for the clinicians performing the follow-up appointments.

Hearing aid settings will be optimised using subjective participant feedback to balance overall volume, perceived sound quality, and perception of own voice/occlusion. This process will follow an interview-style approach, with the participant asked to comment on each component and the clinician making small adjustments to the hearing aid settings until the participant is satisfied with the sound. The hearing aid setting will then be stored and the hearing aids retained at the clinic.

Participants will be required to have an app installed on their smartphone or tablet before the remote hearing aid fitting appointment. They will be guided through this process at the end of the initial in-clinic fitting appointment.

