#### Initial remote hearing aid fitting

Approximately 2 weeks after the in-clinic hearing aid fitting, a remote hearing aid fitting appointment will take place. The time interval is to allow participants’ memory of the sound of the in-clinic programming to decay so that it is less likely to influence the remote fitting. The same hearing aids used at the in-clinic hearing aid fitting will be reset in-clinic and programmed through hearing aid software to 100% acclimatisation using NAL-NL2 prescription targets for long-term hearing aid wearers. The hearing aids will be programmed to allow for a remote hearing aid connection.

The hearing aids will be sent to the participant via courier.

At the scheduled hearing aid fitting appointment time, the clinician will telephone the participant to confirm the app installation and Bluetooth pairing was successful. The participant and clinician will then connect through the app for a remote support session.

Remote support allows an audio–video link between the participant and clinician. The clinician will connect to the participant’s hearing aids through a Bluetooth connection with the participant’s smartphone or tablet.

When both the participant and the clinician are connected to the remote support appointment, the clinician will perform proxy verification measurements through the hearing aid manufacturer software.

Hearing aid settings will be optimised using subjective participant feedback to balance overall volume, perceived sound quality, and perception of own voice/occlusion. This process will follow an interview-style approach, with the participant asked to comment on each component and the clinician making small adjustments to the hearing aid settings until the participant is happy with the sound.

The hearing aid settings will be saved, and the participant will return the hearing aids to the clinic through return-post courier.

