#### Group allocation

Participants will be randomly assigned to one of two groups (“Group A” and “Group B”). Group A will test the remotely fit hearing aids first, followed by the in-clinic fit hearing aids. Group B will test the in-clinic fit hearing aids first, followed by the remotely fit hearing aids. The participants will be blind to group and order of hearing aids, as will the clinician performing follow-up appointments and assessments.

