### Outcomes {12}

Participants will attend an in-clinic appointment to measure outcomes. Outcome measurements will occur in weeks 8 and 14 (4 weeks after the start of each intervention period). The purpose of the crossover design is to overcome the order effects, so the outcomes for the two time points will be combined within the treatment groups.

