## Assignment of interventions: blinding

### Who will be blinded {17a}

This is a double-blind study. Both the participants and the clinicians will be blind to the allocation of groups and order of intervention. The hearing aid settings and real-ear measurements will be stored anonymously so that the clinician is unable to determine what fitting process was used. The participants and clinicians will be aware of the intervention strategy at the fitting process (in-clinic or remote), which occurs prior to group allocation and blinding.

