### Methods in analysis to handle protocol non-adherence and any statistical methods to handle missing data {20c}

All treatment evaluations will be performed on the principle of intention-to-treat (ITT), using the observed data collected from all randomised participants. We do not anticipate a large number of participants with missing data due to the nature of the study procedures. Cases will be excluded for analyses where data are missing. Reasons for missing data will be described if known.

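### Only people who complete both fittings are randomised, and in-clinic fitting always comes first, so failed remote fittings are counted nowhere and fitting order cannot be separated from method

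*Protocol article*

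**What the plan says.** All references are to the protocol article.

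- **Who is randomised.** Implementation {16c}: "All participants who meet the eligibility criteria and complete the in-clinic and remote hearing aid fitting process will be randomised". Who will be blinded {17a} confirms the sequence, describing the fitting process as one "which occurs prior to group allocation and blinding".
- **Who is analysed.** Section {20c} applies intention-to-treat "using the observed data collected from all randomised participants", and excludes cases with missing data.
- **Order of the fittings.** Initial remote hearing aid fitting: "Approximately 2 weeks after the in-clinic hearing aid fitting, a remote hearing aid fitting appointment will take place". According to the article, this gap will "allow participants’ memory of the sound of the in-clinic programming to decay so that it is less likely to influence the remote fitting". Before the remote session, the aids are reset to the prescription.
- **What is randomised.** Group allocation concerns wearing order: "Group A will test the remotely fit hearing aids first, followed by the in-clinic fit hearing aids", with Group B in reverse.
- **What carries over from the clinic visit.** The receiver and dome are chosen at the in-clinic fitting and are to "be consistent for each participant for the duration of the study". Participants are also helped with installing the app at that visit.
- **What the trial is for.** Trial design {8} describes a non-inferiority crossover evaluating teleaudiology as a way of programming hearing aids.

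**The concern.** The intervention under test is the fitting session, and it takes place before randomisation. Two things follow.

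First, the analysis is conditional on the remote session having worked. The remote route has steps that the in-clinic fitting lacks: courier delivery, Bluetooth pairing with the participant's device, and a working audio-video link. If one of these cannot be made to work, the participant is not randomised and contributes to no primary or secondary outcome. Process acceptability does not fill the gap, because outcomes are taken at weeks 8 and 14, which non-completers never reach.

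Second, every remote fitting is a second fitting. The participant has already heard the verified in-clinic sound and has been through the same feedback interview. The article itself recognises that memory of the first sound could influence the second fitting. It does not say whether the remote-fitting clinician can see the in-clinic settings or real-ear record. If either influence draws the remote settings towards the in-clinic ones, the measured difference shrinks. In a trial looking for a difference below a 5 dB limit, that helps a finding of non-inferiority.

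**Working it through.** **Completion: what the plan's own figures cover.** Sample size {14} gives 54 participants, 60 after a 10% attrition allowance: 54 / (1 − 0.10) = 60. This agrees with the stated 60. The article gives no figure for fittings that cannot be completed, so a range has to be assumed.

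**Head-count outside the analysis.** With f the assumed share of participants whose remote fitting cannot be completed, the number left out when 60 are randomised is 60 / (1 − f) − 60.

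| Assumed f | 60 / (1 − f) | Left out |
|---|---|---|
| 5% | 63.2 | 3.2 |
| 10% | 66.7 | 6.7 |
| 20% | 75.0 | 15.0 |

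These are counts of people, not estimates of bias in 4FREAR.

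**Fitting order against method.** The four sequence-by-period cells, from Group allocation and the two initial fitting sections, are:

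| Group | Wearing period | Method worn | Fitted first or second |
|---|---|---|---|
| A | 1 | remote | second |
| A | 2 | in-clinic | first |
| B | 1 | in-clinic | first |
| B | 2 | remote | second |

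Each method appears once in each wearing period, so wearing order is balanced. The last two columns are identical in content: remote always means fitted second. A fitting-order term would duplicate the method term, so no model can estimate the two separately.

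**What carry-over could do.** Let D be the difference that independent fittings would give, and L the share by which the second fitting is pulled towards the first. The observed difference is D × (1 − L). The documents give neither value. As an illustration with assumed values, D = 6.0 dB and L = 0.20 give 6.0 × 0.80 = 4.8 dB, which moves a difference from outside the 5 dB limit to inside it. With L = 0.10 the result is 5.4 dB, still outside.

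The factor (1 − L) is the same whichever fitting comes first. Randomising fitting order would separate an additive order effect but would not remove this shrinkage.

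**The case against.** The strongest reply is that randomising after both fittings is built into the design. Both stored settings must exist before blinded wear can begin, and a person without a remote setting has no paired 4FREAR difference to analyse. Randomising earlier would not rescue that case, since {20c} excludes missing data. This stands, and it is why the remedy is to count completion rather than to move randomisation.

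The article also contains real safeguards. Eligibility requires a compatible device and a minimum connection speed, with a phone lent if needed. App installation is guided, and app and pairing are checked by telephone before the session. Against carry-over, exposure to the in-clinic sound is one appointment, the aids are kept at the clinic and then reset, and in both wearing periods a blinded clinician adjusts the settings before outcomes are measured. These make failures rarer and carry-over smaller. They neither count the failures that remain nor separate order from method.

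A file-access rule may exist in a full protocol that is not shown. That is fair. The article's provisions on de-identified files and anonymous storage, however, serve to hide group and fitting process after allocation, and do not clearly reach the fitting stage.

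Three stronger readings are tempting and are not supported:

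- A reader might infer that both features demonstrably favour remote fitting. The direction is an inference. Nothing in the article links a connection failure to a dB difference, in-clinic non-completers are excluded by the same rule, and rehearsing the interview could conceivably widen the difference.
- A reader might take the statement in Outcomes {12}, "The purpose of the crossover design is to overcome the order effects", as a false claim about the fittings. In context it concerns the two outcome time points, hence wearing order, where it is sound.
- A reader might suppose that dissatisfied participants are dropped. The article gives no such rule; settings are adjusted until the participant is content.

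**Conclusion.** The point holds on the text. Non-completers of the remote fitting enter no planned outcome, and fitting order is wholly aliased with fitting method. The first limits what the trial can say about remote fitting as a service. The second means that the 4FREAR comparison describes a remote fitting made after an in-clinic one, with the receiver and dome already chosen there.

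The size is unknown. The 3, 7 or 15 uncounted people rest on assumed failure rates of 5%, 10% and 20%. The 6.0 to 4.8 dB example rests on an assumed pull of 20%. Shrinkage of the 4FREAR difference is the plausible direction, since it follows from the mechanism that the article names, but it is not demonstrated, and it is less certain for subjective outcomes. The wearing-order crossover itself is not in question.

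**What to change.** 1. **Denominator and completion.** Use all eligible consenting participants as the reporting denominator. Add completion of each fitting mode as a secondary outcome, with reasons for failure, compared by a paired exact test with a confidence interval. Because the remote session always comes second, the reasons should distinguish technical failure from withdrawal before the session. Cost: a log and one extra analysis.
2. **Access.** State that the clinician performing the remote fitting may not open the in-clinic settings or real-ear record. Cost: a file-access rule. This closes the clinician's route for carry-over; the participant's memory remains.
3. **Scope.** State that the 4FREAR conclusion applies to people who completed both fittings after a prior in-clinic fitting. Cost: a narrower conclusion than the Objectives and Discussion suggest.

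Randomising fitting order is not proposed. It would add a clinic visit for about half the participants and, as shown above, would leave shrinkage from carry-over in place.
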